### 2.5. Assessments

The baseline assessment (T0), before participating in the intervention program, will be performed by a neuropsychologist in the Cancer Comprehensive center and the follow-up assessment after the 3-month intervention program (T1), on-site or at home, based on the patient’s preference. The MoCA test will be performed at baseline (inclusion criteria).

Objective cognitive function will be assessed at T0 and T1 with the computerized neurocognitive test battery CNS Vital Sign [56]. This battery uses computerized forms of traditional tests such as symbol digit coding, the Stroop test and finger tapping and has also the capacity to automatically quantify “speed factor” via multiple parameters such as reaction time, psychomotor speed and processing speed. Test-retest reliability, concurrent validity with traditional tests and discriminant validity was assessed and showed similar characteristics to the traditional neuropsychological tests [56]. In this study, we will use the 7 main tests of this battery (30 min):Verbal Memory (VBM), which investigates word recognition and words memorization ability (immediate and delayed recall);Visual Memory (VIM), which investigates recognition and memorization of geometric shapes (immediate and delayed recall);Finger Tapping (FTT), for motor speed and fine motor control assessment;Symbol Digit (SDC) to investigate information processing speed, complex attention, visual-perceptual speed and complex information processing speed-accuracy;Stroop test (ST) for simple and complex reaction time, inhibition/disinhibition abilities, processing speed and frontal or executive skills assessment;Shifting Attention (SAT) to assess executive functions, decision making and reaction time;Continuous Performance (CPT) for sustained attention, impulsivity and choice reaction time.

Subjective cognitive complaints will be evaluated at T0 and T1 through the self-report questionnaire FACT-Cog, which is validated in French, with normative data, and has 4 subscales: Perceived Cognitive Impairments (PCI), Impact on Quality of Life (QoL), Comments from Others (Oth), and Perceived Cognitive Abilities (PCA) [53,57].

To explore the potential secondary effects of the intervention, the following will be assessed at T0 and T1: anxiety and depression will be assessed with the Hospital Anxiety and Depression Scale (HADS) [58], fatigue with the Functional Assessment of Chronic Illness Therapy-Fatigue (FACIT-Fatigue) [59], and quality of sleep with the Insomnia Severity Index (ISI) [60]. Patients’ satisfaction will be evaluated at T1 through a 13-items self-report questionnaire developed in our institution for this study. The questionnaire focuses on patients’ general appreciation on the program; on frequency, difficulty, contents and length of physical and cognitive sessions; software’s easiness of use; the time of the proposed study. Each question has 4 possible answers (from not satisfied at all, to very satisfied) (see Supplementary Material).

Data collection information is summarized in Table 1.

### 2.6. The Multimodal Web-Based Intervention

All participants will be enrolled in a web-home-based multimodal intervention for 12 weeks and will be asked to perform two 20-min sessions of cognitive stimulation per week and two 30-min sessions of APA per week (Figure 1).

After inclusion in the study, participants will meet a neuropsychologist who will introduce and explain to them the 2 online platforms and will give them all the needed materials. A starter kit will be provided at that moment, including a heart rate monitor to adapt the activity during the APA sessions as well as a webcam (if necessary) for the video-conference sessions. This meeting will allow participants to familiarize themselves with all instruments of the study and with the person with whom they will be in contact during the study.

Furthermore, an APA specialist will conduct an initial physical activity interview (45-to-60-min) during which he/she will present the program to the patient and check the patient’s availability for APA sessions and medical contraindications to adapt the sessions according to the needs and constraints of the patients.

#### 2.6.1. Cognitive Stimulation—HappyNeuron Platform^®^

Cognitive stimulation will be remotely provided with the HAPPYNeuron^®^ PRESCO online program (https://www.happyneuronpro.com/, accessed on 27 September 2021) This software has been developed by a neurologist and it is available in 11 languages allowing a comparison of results between international studies. It has already been used in several clinical studies, mainly in the psychiatric field, and in a study with breast cancer patients [47]. This home-based program trains 12 cognitive domains, especially attention, memory, executive functions and processing speed—which are the most impaired after cancer treatments [2] and included 41 different exercises and 9 difficulty levels. This program is particularly appropriate for an interventional study because it allows a standardized intervention targeting a wide range of cognitive domains impaired by cancer treatments (Table 2). Moreover, its user-friendly and intuitive interface, along with its ludic component, may help maintaining patients’ motivation and their adherence to the program.

Participants will have access to the training session through a link sent by e-mail and will have access to it until they receive another mail with the next planned session. All patients will start with the first difficulty’s level, which will increase accordingly with their performance during exercises. Patients will reach the next level after two successful repetitions of the exercise at the given level. Instructions and demonstrations precede each exercise as well as a test to verify if instructions have been well understood. Automatic feedback is generated after each exercise to congratulate patients or to encourage them to persevere if they fail. When starting a new session, patients will carry on at the level they stopped during the previous session.

The neuropsychologist will have access to patients’ results to estimate the evolution of their performance and to verify the frequency with which sessions are being completed. The neuropsychologist also will perform a weekly check for patients’ achievement to the cognitive stimulation program and in case of non-achievement of two following sessions, he/she will contact the patient to verify reasons of non-achievement.

#### 2.6.2. Adapted Physical Activity Training—Mooven^®^ Platform

Participants will access adapted physical activity sessions through the online platform “Mooven^®^” (https://mooven.app/, accessed on 27 September 2021). It is currently involved in more than 15 projects, including a trial with cancer patients.

Participants will schedule two 30-min sessions per week with an APA specialist who will remotely supervise the session through a video-conference system. APA sessions will be standardized and will consist of a warm-up (5 min), endurance/cardio or muscle-strengthening activities (20 min) and then stretching (5 min), as recommended by the French National Cancer Institute [61]. The content of the sessions will be adapted to breast cancer patients [62,63] and if necessary, to their constraints and medical contraindications. Patients’ heartbeat will be constantly monitored using a wrist heart rate monitor and data will be updated in patients’ profile. Furthermore, patients’ rating of perceived exertion will be measured by the Borg rating of the perceived exertion scale [64]. This scale ranges from 6 (no exertion at all) to 20 (maximal exertion).

Patients will have access to their calendar with the next planned video-conference sessions. In case of patient’s inability to attend the video call with the APA specialist, the latter will submit a description of the session to be carried out in autonomy (video supports or sheets) and will contact them after the session to collect the difficulties encountered by the patients through a phone-administered questionnaire. The APA specialist will also report reasons for non-achievement if these do occur.

### 2.7. Statistical Analysis

For the pilot/feasibility study, the inclusion of 20 patients is needed to meet the main objective of evaluating adherence of breast cancer patients with cognitive complaints undergoing radiotherapy to a 12-weeks intervention combining web-based cognitive stimulation and web-based adapted physical activity. A sample size of 20 patients to be enrolled (including the augmentation to anticipate a maximum of 10% of patients with non-evaluable data) will allow estimation with a 95% confidence interval of width +/− 20% an adherence rate of at least 70%.

We expect to reach an adherence rate of 70% (to the APA sessions and the cognitive training sessions) in the present study. Completed sessions and duration will be checked by the neuropsychologist from the patients’ statistics in the HAPPYNeuron^®^ platform regarding cognitive training. Regarding APA sessions, the APA specialist will collect the information directly from patients’ feedback after each session and will confront this self-reported information to those collected by the pedometer (objective measure).

Analysis of non-eligibility motives and factors associated with participation (through data collected by the neuropsychologist at baseline and the coach during the follow-up) as well as analysis of the satisfaction questionnaire will enable us to raise potential limitations of the program such as:social barriers (patients living in remote areas with a poor internet connection, patients with limited access to computer material or low skills in informatics, etc., resulting in selection bias of more affluent women and social inequalities in the access to the program),technological barriers (patients with limited skills in informatics, inappropriate material),or availability barriers (already in an APA or cognitive training program, program too demanding/exhausting, not available enough to complete it, not the good time during cancer therapeutic management to propose cognitive management, etc.).

These key elements will be crucial to identify potential improvements and adjustments of the intervention design for the next steps to develop a randomized study.

Data analysis will be based on the data obtained from the total population (“intent to treat” analysis) enrolled in the protocol. Exploratory data analyses will provide, for qualitative variables, the frequencies and their exact 95% confidence interval (binomial law); for quantitative variables, the mean, the standard deviation of the mean, the median and the quartiles. The demographic, clinical and biological characteristics of the patients will be described using the “intention-to-treat” population. Whenever possible, non-parametric tests will be used. The adherence of breast cancer patients to cognitive stimulation sessions coupled with adapted physical activity will be described in detail as well as the reasons for non-acceptance of the study.

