### 2.2. Objectives

#### 2.2.1. Primary Outcome

The main objective of the Cog-Stim study is to evaluate adherence of breast cancer patients with cognitive complaints undergoing radiotherapy to a 12-weeks intervention combining web-based cognitive stimulation and web-based adapted physical activity. A patient will be considered as adherent to the 12-weeks intervention if 70% of the planned sessions or more are realized. A session will be considered performed if at least 70% of the session has been completed.

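### Minor misstatement of precision: 20 enrolled patients contain no 10% allowance, and ±20 points at 70% adherence is met neither with 18 evaluable nor by the exact interval the plan names

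*Protocol article*

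**What the plan says.** All of this is in the protocol article, mostly in section 2.7 (Statistical Analysis).

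- **Size and allowance.** "A sample size of 20 patients to be enrolled" is the stated number, "including the augmentation to anticipate a maximum of 10% of patients with non-evaluable data".
- **Precision claimed.** That number "will allow estimation with a 95% confidence interval of width +/− 20% an adherence rate of at least 70" per cent.
- **Expected rate.** "We expect to reach an adherence rate of 70" per cent, so 70% is the planning value as well as the bottom of the range claimed.
- **Endpoint (section 2.2.1).** "A patient will be considered as adherent to the 12-weeks intervention if 70% of the planned sessions or more are realized". Each patient is therefore adherent or not, and the primary estimate is a single binomial proportion.
- **Interval method.** The descriptive analyses will give "for qualitative variables, the frequencies and their exact 95% confidence interval (binomial law"). No other interval is named, and the method behind the sample size is not stated.
- **Analysis population.** "Data analysis will be based on the data obtained from the total population (“intent to treat” analysis) enrolled in the protocol".

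**The concern.** If 20 already includes a 10% loss, the ±20 points must hold with 20 × 0.90 = 18 evaluable patients. Yet 20 is close to what the usual normal-approximation formula gives for ±20 points at 70% with no loss at all, so the allowance seems to have been named but not added. In addition, the interval to be reported is the exact binomial one. It is wider than the normal approximation at this size and is not symmetric around the estimate.

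The sentence is the only justification of the sample size and the only property stated for the primary estimate. A reader who takes it at face value expects an observed 70% to come with a lower limit near 50%. The planned interval goes lower than that.

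**Working it through.** **Inputs.** Enrolled 20; non-evaluable at most 10%, so 18 evaluable; confidence level 95% (z = 1.96); target half-width d = 0.20; p = 0.70; exact binomial interval. All are from section 2.7. The endpoint is binary (section 2.2.1).

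**1. Reproducing the plan's figure (normal approximation).**

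n = z² p(1 − p) / d² = 1.96² × 0.70 × 0.30 / 0.20² = 20.17, so 21 evaluable patients after rounding up.

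The stated 20 matches this only before any allowance, and only if 20.17 is rounded down. With the 10% added, 20.17 / 0.90 = 22.4 (23 enrolled), or 21 / 0.90 = 23.3 (24 enrolled).

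**2. Half-width that the stated numbers give (normal approximation).** Half-width = 1.96 × √(p(1 − p)/n).

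| n | p | Half-width (points) |
|---|---|---|
| 18 | 0.70 | 21.2 |
| 20 | 0.70 | 20.1 |
| 21 | 0.70 | 19.6 |
| 18 | 0.75 | 20.0 |

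With 18 evaluable, the claim becomes true only from about 75% adherence.

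**3. The interval the plan names (exact binomial, Clopper-Pearson).**

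| Adherent / n | Observed | Exact 95% CI | Below / above (points) | Half the total width (points) |
|---|---|---|---|---|
| 14/20 | 70.0% | 45.7% to 88.1% | −24.3 / +18.1 | 21.2 |
| 16/20 | 80.0% | 56.3% to 94.3% | −23.7 / +14.3 | 19.0 |
| 12/18 | 66.7% | 41.0% to 86.7% | −25.7 / +20.0 | 22.8 |
| 13/18 | 72.2% | 46.5% to 90.3% | −25.7 / +18.1 | 21.9 |
| 14/18 | 77.8% | 52.4% to 93.6% | −25.4 / +15.8 | 20.6 |
| 15/18 | 83.3% | 58.6% to 96.4% | −24.8 / +13.1 | 18.9 |

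Exactly 70% cannot be observed with 18 patients; 13/18 is the nearest result above it. Half the total width falls within 20 points from 15/18 or from 16/20 upward, but not at 70%.

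**4. Could another method give 20?** A Wilson interval at 70% with 18 patients has a total width of 39.1 points, which would fit 18 evaluable and 20 enrolled. The article does not name it, and it runs −23.1/+16.0 around 70%, which is not ±20.

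**The case against.** Four arguments for the plan deserve an answer.

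- **All 20 patients count.** The analysis is by intention to treat on everyone enrolled. On that reading the normal approximation gives 20.1 points, which rounds to the stated figure. This stands as far as it goes. It leaves the allowance for non-evaluable data without a purpose, however, and the exact interval at 14/20 still misses.
- **The claim is for at least 70%.** Precision improves above that, and from about 75% the normal approximation with 18 patients meets the target. True, but the claim includes 70%, and 70% is the rate the plan expects.
- **The exact interval is mentioned under exploratory analyses.** Planning with an approximation and reporting an exact interval is common practice. That is fair, and it softens the second part of the point. The missing allowance does not depend on it.
- **The excess is small.** Measured as half the total width, the shortfall near 70% is 0.1 to 1.2 points (normal) or 1.2 to 1.9 points (exact). This stands, and it sets the severity.

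A reader might also infer that the lower limit decides whether the randomised study goes ahead. The article does not say so. It sets no progression threshold and no test against 70%; it states an expectation, and says that the pilot results will be used to adjust the design of a randomised study that will follow. Nor does the error call for a success rule such as at least 14 adherent of 20. That would be a new rule, and it would sit badly with 18 evaluable, where 13/18 is already above 70%. Finally, the 24 to 26 point figures are lower arms. Reading ±20 as a limit on each arm separately is stricter than the text requires, since an asymmetric interval cannot be symmetric around its estimate.

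**Conclusion.** The precision statement is wrong as written, and the error is minor. The figure of 20 is the normal-approximation number without the 10% allowance that the article says it includes; with the allowance it would be 23 or 24. With 18 evaluable the half-width at 70% is 21.2 points instead of 20. The exact interval has a half-width of 21.2 points at 14/20 and 21.9 at 13/18, with lower limits of about 46% in both cases.

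This rests on three assumptions: that ±20% means a half-width of 20 percentage points; that the allowance leaves 18 evaluable patients; and that the primary proportion will get the exact interval, as the only one named. If all 20 patients are counted and the normal approximation is used, the shortfall disappears on rounding. The endpoint, the conduct of the study and its usefulness as a feasibility study are not affected.

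**What to change.** Keep 20 patients and replace the precision sentence in section 2.7 with one that states what they give, for example: *With 20 patients and 14 adherent (70%), the exact 95% confidence interval is 45.7% to 88.1%; with 18 evaluable and 13 adherent (72.2%), it is 46.5% to 90.3%.* Delete the statement that ±20% holds after a 10% loss. In the same place, say whether non-evaluable patients stay in the denominator, so that the allowance and the intention-to-treat sentence agree.

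The cost is a sentence or two and a slightly less favourable stated precision. Recruitment, endpoint and analysis do not change. The alternative of keeping ±20 points with the allowance would mean enrolling 23 or 24 under the normal approximation. For a feasibility study, restating the precision is the proportionate choice.

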## 3. Discussion

Breast Cancer patients are actively demanding interventions to improve their cancer-related cognitive impairment [14,65]. Nevertheless, without available and validated guidelines for the management of cognitive complaints, only 30% of patients receive the help demanded for their cognitive impairment [66]. While the beneficial effects of both cognitive stimulation and physical activity have been proved [2,23,24,25,26], many barriers limit the setup of such interventions in supportive care units in hospitals. Web-based interventions have been used to reduce some of these barriers, including the cost of interventions, while increasing convenience for patients, also reaching patients who are normally isolated and cannot benefit from these interventions [67] and have resulted as efficient in the improvement of CRCI [44,45,46,47,48,49,50]. Nevertheless, little is known about patients’ preferences in terms of length of the program, length, and frequency of the sessions. This pilot study aims to bridge this gap, collecting patients’ opinion on this topic. Thereafter, based on the results from this pilot study, a multisite randomized controlled study will be conducted, to identify the best computerized intervention for the improvement of CRCI.

The web-based/home-based nature of the Cog-Stim study program will allow a generalization of this intervention for all cancer patients with cognitive complaints. This will provide better support for cancer patients with cognitive difficulties by helping them go back more smoothly to daily living activities, social interactions and work, thus improving their quality of life during and after cancer treatments. The value of such interventions has also increased with the COVID-19 outbreak, during which, thanks to web-based approaches, it has been possible to provide remote support.

## 4. Conclusions

The efficacy of web-based cognitive stimulation and physical activity has been demonstrated, but the added value of a combination of these interventions needs to be more investigated. This study will assess the acceptability and feasibility of such combined intervention using web-based platforms in breast cancer patients with cognitive complaints. The data collected from the Cog-Stim study will be the base for the development of a personalized combined intervention to help patients to cope with CRCI.

## Figures and Tables

**Figure 1 cancers-13-04868-f001:**
[figure not shown]
Study flowchart. APA: adapted physical activity.

**Table 1 cancers-13-04868-t001:** Details concerning data collection.

Data Collection	Before Inclusion	Baseline Assessment (T0)	Assessment Post-Intervention (T1)
Signature of Informed Consent			
Clinical Examination Including medical history ECOG and vital signs			
Cognitive Assessment AND Quality of Life Questionnaires			
FACT-COG			
MoCA			
CNS Vital signs battery			
HADS, FACIT-F, ISI			
Patient’s Satisfaction			

ECOG: Scale of Performance Status; FACT-COG: Functional Assessment of Cancer Therapy—Cognitive Function; MoCA: Montreal Cognitive Asessment; HADS: Hospital Anxiety and Depresion Scale; FACIT-F: The Functional Assessment of Chronic Illness Therapy—Fatigue; ISI: Insomnia Severity Index.

**Table 2 cancers-13-04868-t002:** HappyNeuron^®^ exercises used for cognitive stimulation.

Cognitive Domains Trained	Exercises
Memory (Verbal and Visual)	Words, Where are you? Elephant Memory Shapes and Colours Heraldry Displaced Characters Displaced Images N-Back Around the World in 80 trips I Remember You! Restaurant An American in Paris Find Your Way! Chunking Objects, Where are You?
Executive functions	Towers of Hanoi
	Basketball in New-York
	Hurry for Change!
Attention	Pay Attention!
	Private Eye!
	Sound Check!
	Ancient Writing
Information processing speed	Two-Timing
	Under Pressure
	Gulf Stream
	Catch the Ladybug!
Language	Split words
	Embroidery
	Secret files
	Speak Your Mind!
	Decipher
	Writing in the Stars
	This Story is Full of Blanks!
	Which One is Alike?
Logic	The Right Count
	Countdown
	Ready, Steady, Count!
visuospatial abilities	Sleight of Hands
	Entangled Figures
	Point of View
	Turn Around and Around

## Data Availability

The data presented in this study are available on request from the corresponding author. The data are not publicly available accordingly to good clinical practice (GCP) guidelines.
